## Abstract

**Background:** Individuals with obesity are known to present cognitive deficits, especially in executive functions. Executive functions play an important role in health and success throughout the whole life and have been related to food decision-making and to the ability to maintain energy balance. It is possible to improve executive functions through targeted training. This would involve brain plasticity changes that could be studied through connectivity MRI. The general hypothesis of this study is that executive functions training in children with obesity can improve food choices and produce cognitive and neuroimaging changes (structural and functional connectivity), as well as improve emotional state and quality of life.

**Methods:** Randomized controlled double-blind trial with 12-month follow-up. Thirty children with obesity will be randomly allocated into “executive training” (Cognifit with adaptive difficulty + Cogmed) or “control task” group (Cognifit without adaptive difficulty). Both groups will attend 30–45 min of individual gamified training (Cogmed and/or Cognifit systems) by iPad, five times per week during 6 weeks. Cogmed and Cognifit software are commercially available from Pearson and Cognifit, respectively. Participants will receive an iPad with both apps installed for a 6-week use. Participants will also receive counseling diet information via presentations sent to the iPad and will wear a Fitbit Flex 2 tracker to monitor daily activity and sleep patterns. Main outcomes will be cognitive, emotional, food decision, and quality-of-life measures, as well as neuroimaging measures. Participants are evaluated at baseline (T0), after treatment (T1), and 12 months since baseline (T2).

**Discussion:** Longitudinal study with active control group and 3 time points: baseline, immediately after treatment, and 1 year after baseline. Threefold treatment: executive function training, psychoeducation, and feedback on activity/sleep tracking. We will evaluate the transfer effects of the intervention, including emotional and functional outcomes, as well as the effects on neural plasticity by connectivity MRI.

**Trial registration:** This project has been registered in ClinicalTrials.gov (trial registration number NCT03615274), August 3, 2018.

## Introduction

Childhood obesity is one of the most serious public health challenges of the 21st century. Its prevalence has increased at an alarming rate. Globally, in 2016 the number of children with overweight under the age of 5 was estimated to be over 41 million (1). Children with overweight or obesity are likely to stay obese into adulthood and more likely to develop noncommunicable diseases like type 2 diabetes and cardiovascular diseases at a younger age. Overweight and obesity, as well as their related diseases, are largely preventable. Prevention of childhood obesity, therefore, needs high priority (1). Furthermore, childhood obesity has long-term complications such as psychosocial and psychological problems (i.e., depression and low self-esteem) (2, 3).

Weight-loss programs in children have shown limited success, especially at long term (4). A better comprehension of vulnerability factors related to weight gain should provide valuable information for designing more effective treatments (5). In obesity, there is an imbalance between ingested and expended calories (6). On one hand, there is increased availability of energy-dense food that is high in fat; on the other hand, there is a decrease in physical activity. Therefore, novel interventions addressing both aspects of the problem are needed. Guidelines state that “treatment should focus on reducing caloric intake, increasing physical activity, modifying behavior (motivation and readiness to make behavioral and dietary changes), and including family members as active treatment participants” (2).

In addition, individuals with obesity have significant cognitive deficits, especially in executive functions (7). Executive functions are neuropsychological processes including decision-making, inhibitory control, and working memory. All of them are highly implicated in the cognitive control of eating impulses and in the ability to maintain energy balance, as well as in the motivation and adherence to a reduced-energy diet (8, 9). Inhibitory control is the most consistently reported to be impaired, although there is also impairment in reward sensitivity, attention/set-shifting, and working memory (10). Executive impairment also seems to be on the basis of some of the behaviors characteristic of obesity (i.e., increased food intake, disinhibited eating, and less physical activity). Therefore, it is a relevant factor to be considered in weight-loss interventions (11).

The mechanism by which obesity is associated with cognitive function is not clear yet. Smith et al. (12) suggested a bidirectional relationship, where obesity impairs executive functions by affecting cerebral tissue/mechanisms (such as brain inflammation and/or glucose abnormalities), and this impairment in executive functions has an influence in turn on obesity by causing an inability to regulate food intake, plan ahead, and inhibit responses and by promoting impulsive behavior (13, 14). If obesity exerts a detrimental effect on the brain, it is important to prevent obesity during brain development, particularly during the development of executive functions (10) that begins in early childhood and continues in adolescence, and has been attributed to the maturation of the prefrontal cortex (15).

It is possible to improve executive functions through targeted training. This targeted intensive cognitive training induces more effective neural system operations, providing cerebral plasticity (16). Executive functions and working memory training with game elements significantly improved working memory, but also motivation, training performance, and school performance in low-attending children (17, 18).

MRI can be used to assess changes in brain activity induced by training. Several weeks of daily executive function training enhanced working memory–related activity in middle frontal and intraparietal areas (19) and also produced changes in cortical thickness in young adults (20), thus showing that the neural systems underlying executive functions are plastic (21). Brain connectivity changes after training have also been reported in children (17) and adults (22, 23), and could predict body mass index (BMI) (24). However, even if neuroimaging could be a potential biomarker of responsiveness to treatment, changes in connectivity after obesity treatment (including cognitive training) have not been explored yet.

Lastly, children with obesity may experience more psychological disorders (self-concept, anxiety, and depression) (3) and reduced scores in quality of life (QoL) measures than normal-weight children (25). Treating executive deficits while fostering physical activity and promoting healthy nutritional habits may also help to improve QoL and emotional state.

This project has the purpose of evaluating the impact of executive functions training in BMI, food choice, and cognition in children with obesity as well as in their emotional state and QoL. These changes are expected to induce cerebral plasticity that will be measured by MRI connectivity. We hypothesize that children with obesity undergoing the cognitive training program will perform better than active controls in cognitive measures, take better food-related decisions, and consequently, show changes in brain connectivity, emotional state, and QoL measures at the end of the intervention and during the follow-up at 12 months. We also expect them to maintain BMI.

## Materials and Methods

### Study Design

The design is a randomized controlled double-blind trial with 12 months of follow-up. Patients meeting study criteria are randomly allocated according to a sequential number into the “executive functions training” or “control task training” groups after given written informed consent to the coordinator of the project ([name]). A sample of the informed consent can be found in Supplementary Material 1. Randomization is stratified by sex, age (9–12 years), and manual dominance. The same person is the one in charge of monitoring training compliance, so the rest of the team is blind to group allocation. All neuropsychological assessments are performed by an independent psychologist ([name]), blinded to group allocation. Patients and families are also blind to the study-group allocation. Because the intervention has no possible side effects, there are no circumstances under which unblinding is permissible. This protocol report follows the SPIRIT and CONSORT reporting guidelines (26, 27).

### Trial Registration Dataset and Protocol Version

The trial has been retrospectively registered in ClinicalTrials.gov (https://clinicaltrials.gov/) on August 3, 2018. The last version of the protocol is the fourth version (March 25, 2020). Table 1 shows the study version history and a summary of the dataset information.

Table 1Trial registration dataset.

**Table d39e458:** 

**Data category**	**Information**
Primary registry and trial identifying number	ClinicalTrials.gov NCT03615274
Date of registration in primary registry	August 3, 2018
Secondary identifying numbers	2016-16-10
Source(s) of monetary or material support	Fundació La Marató de TV3
Primary sponsor	Fundació La Marató de TV3
Contact for public and scientific queries	PI: [name] [name] [contact] Coordinator: [name] [name] [contact] Department of Clinical Psychology and Psychobiology Institut de Neurociències University of Barcelona, Barcelona, Spain, 08035
Public title	Executive Function Training in Childhood Obesity: Food Choice, Quality of Life, and Brain Connectivity (TOuCH)
Scientific title	Executive Function Training in Childhood Obesity: Food Choice, Quality of Life, and Brain Connectivity (TOuCH)
Countries of recruitment	Spain
Health condition(s) or problem(s) studied	Childhood obesity
Intervention(s)	Experimental: experimental
	Active comparator: placebo non-adaptive training
Key inclusion and exclusion criteria	Ages eligible for study: 9–12 years Sexes eligible for study: all Accepts healthy volunteers: no
	Inclusion criteria: being obese according to the criteria by Cole et al. (28)
	Exclusion criteria: neurological, psychiatric, or developmental disorder
Study type	Interventional (clinical trial)
	Allocation: randomized intervention model. Parallel assignment masking: double blind (participant, family, investigator, and outcomes assessor)
	Primary purpose: treatment
Date of first enrollment	Estimated for February 2, 2018
Target sample size	30
Recruitment status	Recruiting
Primary outcome(s)	Change from baseline in cognitive, MRI, food choice, and BMI measures at the end of the intervention and follow-up at 12 months
Key secondary outcomes	Change from baseline in emotional state, physical activity, and quality-of-life measures at the end of the intervention and follow-up at 12 months

**Table d39e603:** 

**Study records version**		
**Version**	**Submitted Date**	**Changes**
1	July 30, 2018	Original version
2	October 14, 2019	Study status
3	November 21, 2019	Eligibility and study status
4	March 25, 2020	Study status

### Ethics Approval and Consent to Participate

Ethics approval was provided by the University of Barcelona Institutional Review Board (IRB00003099 protocol 122/V/2016), and by the Consorci Sanitari de Terrassa (02-17-503-039) and Sant Joan de Deu Hospital (PIC-02-19) Review Boards. The parents or legal tutors of all participants (in the presence of the children) gave written informed consent in accordance with the Declaration of Helsinki before enrollment. The trial has minimal risk because it has no adverse effects and it is based on commercially available training programs. Cogmed and Cognifit are commercially available from Pearson and Cognifit, respectively. Both programs have previous publications guaranteeing their efficacy (*see next point*). Furthermore, the IRB protocol (IRB00003099) from the University of Barcelona ensures that participation is voluntary, that participants could quit at any time they chose, that signed informed consent is obtained, that confidentiality is maintained, and that data security is rigorous. Participants will receive 20every time they come to the MRI to cover the travel expenses.

Any modifications to the protocol, which may impact on the conduct of the study, potential benefit of the patient or may affect patient safety, including changes of study objectives, study design, patient population, sample sizes, study procedures, or significant administrative aspects, will require a formal amendment to the protocol. Such amendment will be approved by the Ethics Committee/Institutional review board before implementation and notified to the participants and families.

### Cogmed and Cognifit Evidence of Efficacy

According to Simons et al. (29) (pp. 143–148), “Cogmed Working Memory Training has been classified as one of the five commercial cognitive-training programs whose effectiveness had been assessed by several publications. The studies investigating the effects of Cogmed working memory training were undoubtedly the most numerous and best designed (e.g., often including active controls).” In addition, a recent independent meta-analysis by Aksayli et al. (30) evaluated the impact of Cogmed on people's cognitive and academic skills as a function of the type of transfer (near- or far-transfer). They used stricter inclusion criteria than previous meta-analysis (i.e., including a control group and excluding studies with subjective measures of cognitive/academic skills) to ensure a minimum standard of quality. They reviewed 50 independent studies, from a total of 2,761 records examined, and concluded that the training program increased performance on memory tasks immediately post-test (Hedge's *g* = 0.444) and this improvement remained significant after several months, although it slightly decreased (*g* = 0.365 at follow-up). Participants improved the most in those memory tasks whose demands and visual stimuli were very similar to the trained tasks (very-near-transfer; *g* = 0.566 and 0.487 immediately post-test and at follow-up, respectively), while there was a moderate effect on the participants' performance on those memory tasks not included in the training program (lesser-near-transfer; *g* = 0.246, *p* = 0.002 and *g* = 0.176, *p* = 0.005 at post-test and follow-up, respectively).

The Cognifit software has been however less studied. There are no independent studies to date including a sample of children. Therefore, we have assessed its efficacy according to independent studies on adult population. In a study by Siberski et al. (31), the effect of cognitive training vs. computer gaming was evaluated, and results showed that Cognifit significantly improved monitoring, planning, recognition, response time, shifting, spatial perception, visual memory, and visual scanning with medium-sized effects (Cohen's d ranged from 0.58 to 0.72) and naming, visual perception, and working memory with small effect sizes (*d* = 0.44, 0.37, and 0.41, respectively). However, the computer games group also showed an improvement in divided attention (Cohen's *d* = 0.85), inhibition (*d* = 0.67), recognition (*d* = 0.64), and updating (*d* = 0.44). In a study by Verghese et al. (32), assessing the effect of cognitive training on physical activity (concretely on gait speed), participants who underwent Cognifit training had an improvement in gait velocity during normal walking (*p* = 0.05; calculated Cohen's *d* = 0.65) and in walking while talking condition (*p* = 0.002; calculated Cohen's *d* = 1.15). Finally, an independent review by Shah et al. (33) classified Cognifit training program as delivering Level I evidence (at least two well-designed randomized control trials or quasi-randomized studies, one with high quality and the other at least of moderate quality as rated on a risk of bias score (PEDro score) and Cogmed as Level II evidence (at least one well-designed randomized control trials of high quality as rated on the PEDro score).

### Study Sample and Setting

Participants will be children with obesity aged 9–12 years followed by an endocrinologist pediatrician at two hospitals located in the area of Barcelona: Consorci Sanitari de Terrassa and Hospital Sant Joan de Déu. We attempt to include children until we have a sample of 30 children with a complete training and post-training visit. The pediatric assessment will consist of height, weight, waist circumference, blood pressure, puberal state, and personal and familial history. Height and weight will be converted into BMI.

Inclusion and exclusion criteria are detailed in Figure 1. Participants should also have a stable wifi connection at home to be able to perform the training. Figure 2 shows the flow diagram of the study recruitment with the sample recruited to date.

**Figure 1 F1:**
[figure not shown]
Diagram of the study protocol methods.

**Figure 2 F2:**
[figure not shown]
CONSORT flow diagram of study recruitment.

#### Sample Size

We attempt to achieve a total sample size of 30 subjects who have completed the treatment (training rate >70% of the days) and with a complete neuropsychological and MRI post-treatment assessment, 15 children per group. Previous literature on the field has shown significant results with similar sample sizes. Boutelle et al. (34) described a significant decrease in the percentage of eating (*d*_ppc2_ = 0.6, medium effect size) and ingested kcal (*d*_ppc2_ = 0.64, medium size), after training attention in a sample of 14 children (vs. 15 children doing a control task), showing far-transfer effect. Also, Verbeken et al. (35) reported a reduction in BMI (at 2-month follow-up; η_p_2 = 0.16, *d*_ppc2_ = 0.20, small effect) and improvement in short-term visual memory (Corsi block tapping task-forward; η_p_2 = 0.13, *d*_ppc2_ = 0.75, large effect), visual working memory (Corsi block-backwards; η_p_2 = 0.14, *d*_ppc2_ = 0.53, medium effect; BRIEF working memory; η_p_2 = 0.10, *d*_ppc2_ = 0.22), and meta-cognition (BRIEF; η_p_2 = 0.12, *d*_ppc2_ = 0.71) after training 22 children with obesity in visual working memory (vs. 22 children in passive control group). Also, Verbeken et al. (36) showed that an inhibition control and attentional training could significantly reduce inhibition problems (BRIEF; η_p_2 = 0.26, *d*_ppc2_ = 1.91, large effect) in a sample of 22 children with obesity (vs. 15 children in the passive control group).

In addition, multidisciplinary behavioral interventions have shown to produce significant decreases in BMI with similar sample sizes. Delgado-Rico et al. (37) showed a decrease in BMI (Cohen's *d* = 0.5, medium effect size) related with a decrease in impulsivity and inhibitory control in 42 adolescents. Also, Melnyk et al. (38) have shown a significant decrease in weight and BMI (large positive effect size, *d* = 1.5; *p* = 0.05) in a sample of 13 adolescents. Vignolo et al. (39) showed a significant reduction in standardized BMI (calculated Cohen's *d* = 1.75, large effect) and adjusted BMI (calculated Cohen's *d* = 0.66, medium effect) after a hospital-based multidisciplinary program, together with a reduction in waist circumference and improved family habits, emotional and social aspects, and motor skills in a sample of 20 children. Moens and Braet (40) showed a reduction in BMI after 6 months of parent-led cognitive-behavioral training in a sample of 31 children vs. 19 at waiting list [*t*_(30)_ = 2.44, *p* = 0.021]. Finally, Gao et al. (41) assessed the effect of home-based *exergaming* (exercise with videogames) in 18 children compared with an active control group (*n* = 16), showing that cognitive flexibility improved (η_p_2 = 0.19, medium effect size).

Regarding computerized cognitive training, especially those targeting working memory, executive function, and inhibitory control (which are the goal of this study), it may exert a positive effect on cognition assessed with similar sample sizes, concretely in visual, and/or verbal working memory at post-treatment (η_p_2 = 0.21; *d*_ppc2_ = 2.43, large effect size) (17, 42) and at follow-up [η_p_2 = 0.18; *d*_ppc2_ = 3.39, large effect size (42); *d*_ppc2_ = 1.51, large effect (43)], in word fluency (*d*_ppc2_ = 0.57, medium effect), in visuospatial complex memory (*d*_ppc2_ = 0.97–1.08, large effect size) (44), in decision-making (healthy food, hypothetical shopping task) (η_p_2 = 0.118, *d*_ppc2_ = 0.65 and 0.44, medium effect), and in healthy food choice (real food task) (*d*_ppc2_ = 0.65, medium effect) (45).

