### Outcomes

We will assess the effect of the intervention on BMI, food choice, global cognition, and neural plasticity. Secondary measures will be emotion/behavior, QoL, and physical activity (see details of the registered protocols in Table 1). There will be three evaluation timepoints: (1) *baseline assessment* (T0); (2) *post-training assessment* (T1), which will be performed after the 6-week training period; and (3) 1-year follow-up assessment (T2), which will be done 12 months after T0, with a leeway of 1 month.

We will collect cognitive, psychological (emotional and quality of life measures), and MRI data in all three time points. Participants' parents will also be interviewed in T0 and T2. Socio-economical data from family, school information, and habits of nutrition and physical exercise from children will be obtained to characterize the sample.

Food, activity, and sleep hours registries will be collected during the 6 weeks of training and for a week at 12-month follow-up.

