#### Additional Analysis: Non-adherence or Missing Data

We will further analyze if discontinuation affects more one of the experimental groups, and we will also evaluate the baseline properties of the subjects that discontinue or perform the intervention at a non-successful level (reaching a number of essays/training days). Missing behavioral data can be handled by multiple imputation. However, in the case of missing, uncompleted, or artifacted MRI data, we will discard these subjects from the group analysis.

Missed trainings will be addressed by an intention-to-treat (ITT) approach to evaluate if they affect the results. Thus, we will analyze the available data by list-wise deletion without imputing the unknown values.

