## Details of the Sample Enrollment to Date

A total of 263 children and their families were contacted to participate in the study from the two areas covered by the two participating hospitals. From those, a total of 44 children and their families (16.73%) consented to participate in the study and underwent the first neuropsychological assessment. A total of 16 families are still pending on taking a decision regarding if participating or not; 100 did not meet the inclusion criteria, 65 families refused to participate in the study, and 38 families did not answer to our calls. From the 44 subjects assessed neuropsychologically, 3 children did not meet inclusion criteria for cognitive impairment, and 2 did not perform the MRI assessment. A total of 39 children were therefore randomly assigned to one of the training groups (88.6% of the ones who consented). To date, there are 22 children with a baseline visit in the experimental group and 17 in the control group. From those, 26 children to date completed the training (task completion more than 70%) and have both neuropsychological and MRI post-treatment assessments (66.6%). Five children more underwent only neuropsychological assessment (a total of 79.5%) due to claustrophobia or because of MRI abnormalities. A total of eight children (20.5%) dropped out or did not reach the minimum training requirements (at least a 70% of completion), six in the experimental group and two in the control group. We explain this higher dropout rate in the experimental group due to the increasing difficulty in the training tasks. This results in a 79.5% retention rate with a training completion of at least 70%.

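### The target of 30 counts children who complete more than 70% of training, an event the article itself ties to the experimental arm's difficulty, and the abstract's 30 randomised contradicts it

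*Protocol article*

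**What the plan says.** The Sample Size section gives the target as "We attempt to achieve a total sample size of 30 subjects who have completed the treatment (training rate >70% of the days". Each of these children must also have been assessed after treatment by both neuropsychology and MRI, and the arms are to hold 15 each. Study Sample and Setting turns this into a rule for closing recruitment: "We attempt to include children until we have a sample of 30 children with a complete training and post-training visit". The abstract says something else: "Thirty children with obesity will be randomly allocated into" the two arms. The registration table gives 30 under "Target sample size" without saying 30 of what.

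Details of the Sample Enrollment to Date reports 39 children randomised, 22 experimental and 17 control. Eight dropped out or fell short of the training minimum, six experimental and two control. The article comments: "We explain this higher dropout rate in the experimental group due to the increasing difficulty in the training tasks".

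On analysis, the section on non-adherence and missing data says: "Missed trainings will be addressed by an intention-to-treat (ITT) approach to evaluate if they affect the results". It then describes this as list-wise deletion with no imputation, although the paragraph before it allows multiple imputation of missing behavioural data. The Discontinuation section promises that every child is followed at every time point under the intention-to-treat principle.

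**The concern.** Completing training happens after randomisation. Adaptive difficulty is what the experimental training has and the control training lacks, and the article names rising difficulty as the reason more experimental children fell out. If the main comparison is made in the children who fill the target, the arms are no longer the randomised arms: the experimental arm has been filtered by a feature of its own treatment. A cognitive difference at T1 could then partly reflect who stayed.

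The intention-to-treat wording does not clearly prevent this. One section offers it as a check carried out by deletion. Another promises full follow-up on the same principle. Neither says which children enter the primary analysis.

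The number 30 also means different things in different places, so a reader cannot tell whether the trial has reached its size.

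**Working it through.** **1. The article's own flow figures.** From Details of the Sample Enrollment to Date: 44 + 16 + 100 + 65 + 38 = 263 contacted; 26 + 5 + 8 = 39 randomised; 8/39 = 20.5%; (26 + 5)/39 = 31/39 = 79.5%; 26/39 = 66.7% (printed as 66.6%). All reproduce apart from that truncation. The 31 split by arm as 22 - 6 = 16 and 17 - 2 = 15. The arm split of the 26 with MRI is not given.

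**2. Non-completion by arm.** 6/22 = 27.3% and 2/17 = 11.8%, a difference of 15.5 percentage points. The Newcombe 95% interval is about -11 to +38 points; Fisher's exact p = 0.43.

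**3. Status against 30.**

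| Reading of 30 | Source | To date |
|---|---|---|
| Randomised | Abstract | 39, exceeded |
| Complete training and post-training visit, if a visit without MRI counts | Study Sample and Setting | 31, reached |
| Training, neuropsychology and MRI | Sample Size | 26, four short |

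**4. What each reading implies at the observed rates.** For 15 completers per arm: 15/(1 - 6/22) = 20.6, so 21 experimental; 15/(1 - 2/17) = 17 control; 38 randomised in all. For 30 who also have MRI: 30/(26/39) = 45 randomised. If only 30 are randomised: 30 × 31/39 = about 24 completers, and 30 × 26/39 = 20 with MRI as well.

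**5. How far a completer comparison could mislead.** The documents give no scores for non-completers, so this is a simulation under assumptions. T0 and T1 scores are standard normal with correlation r = 0.6, 0.8 or 0.9, and there is no treatment effect. Arms are 22 and 17, and 6 and 2 children are removed. Experimental losses are drawn with probability proportional to exp(-w × score), with w = 0.5 or 1.5; control losses are random. There are 4,000 runs per scenario. The table shows bias in SD units in favour of training, across the three values of r.

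| Dropout depends on | w | T1 only, unadjusted | Change from T0 | T1 adjusted for T0 |
|---|---|---|---|---|
| T0 score | 0.5 | +0.08 to +0.13 | -0.06 to -0.01 | about 0 |
| T0 score | 1.5 | +0.20 to +0.29 | -0.13 to -0.03 | about 0 |
| T1 ability | 0.5 | about +0.15 | +0.01 to +0.06 | +0.03 to +0.10 |
| T1 ability | 1.5 | about +0.33 | +0.03 to +0.13 | +0.07 to +0.22 |

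With w = 1.5 on T0, type I error of the unadjusted T1 test is about 9 to 14%; with w = 0.5 it is about 6 to 7%. If low scorers are lost in the same way in both arms, the unadjusted T1 bias shrinks to about +0.05 to +0.19. It does not vanish, because the fraction removed still differs between arms. For scale, the article cites g = 0.246 at post-test for memory tasks outside the trained set.

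The group-by-time effect of a repeated-measures model with T0 and T1 is the change-score comparison, so the third numeric column is the closest to the general linear model planned for BMI and cognition. The Data Analysis Plan also mentions t-tests of means, with regression adjustment if confounders are not well controlled.

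**The case against.** The strongest reply is that nothing in the article says the primary analysis is restricted to completers. A target counted in evaluable children is a common way to allow for attrition, the Discontinuation section commits to following everyone, and analysis sets are often defined in a statistical analysis plan, which is not shown. That stands in part: a reader might infer a completers-only primary analysis, and the text does not support going that far. But the article does state its target population, its rule for closing recruitment and its intention-to-treat method, and these do not fit together.

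Other strong readings also fail:

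- **27% against 12% as proven differential loss.** It rests on 8 events and mixes dropout with training below the minimum. Some of those children may still have T1 data. The concern rests on the article's own causal explanation, which is itself a conjecture.
- **A spurious benefit of training.** That holds for an unadjusted T1 comparison under assumed selection. Change scores, closer to the planned model, can be biased against training.
- **Three incompatible targets.** The Outcomes section says: "We will collect cognitive, psychological (emotional and quality of life measures), and MRI data in all three time points". A complete post-training visit can therefore include MRI, and the two body sections may be one rule. Only the abstract plainly contradicts them.
- **Freedom to choose when to stop, or topping up by arm.** No interim look at outcomes is described, everyone but the coordinator is said to be blind, and replacement within arms is only inferred from the 15 per group.

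**Conclusion.** The point holds in limited form and should be fixed. Target and recruitment closure both depend on a post-randomisation event that the article links to the experimental treatment, and the primary population is not secured against selection on that event. How much this matters cannot be settled from the documents. Under no true effect and the selection strengths tried, a completer analysis is biased by about +0.08 to +0.33 SD without adjustment and -0.13 to +0.13 SD for change scores. With baseline adjustment the bias is about 0 if dropout depends only on baseline, and up to about +0.2 SD if it depends on post-training ability. Even the sign therefore depends on the analysis chosen and on why children stop.

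The contradiction over 30 needs no assumption: the abstract conflicts with the Sample Size and Study Sample sections and with the 39 already randomised. Whether a visit without MRI counts (31 against 26 to date) is an ambiguity and not a second contradiction.

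**What to change.** - State that the primary analysis includes all randomised children with outcome data, in their allocated arm whatever their training rate, adjusted for baseline. Replace list-wise deletion with the multiple imputation the article already allows for missing behavioural data. Label the more-than-70% set supplementary.
- Restate the target once, as a number randomised, with the numbers expected to have cognitive and MRI data (31 and 26 of 39 to date). Use it in the abstract, Study Sample and Setting, and Sample Size, and say whether a post-training visit without MRI counts.
- Keep inviting children who stop training to T1 and T2, as the Discontinuation section promises. This matters most: if dropout depends on post-training ability, neither baseline adjustment nor imputation from baseline fully removes the bias, whereas observed outcomes do.

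The cost is wording plus visits already promised. The downside is that the effect in all randomised children may be smaller than the effect in completers.
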